# BACKGROUND

Worldwide, there are 36.7 million people living with HIV (PLWH) with a marked increase in uptake of antiretroviral therapy (ART) and a steep decline in numbers of AIDS-related deaths. However globally the leading cause of death is from cardiovascular disease (CVD) with the majority of deaths occurring in developing countries. The path to atherosclerotic CVD progression, mainly coronary artery and cerebrovascular disease, remains silent until advanced stages and the end result is significant disability or death.

An estimated 16.6% of South Africans aged between 15-49 years are living with HIV, of which 23.2% are women of reproductive age. A reduction in HIV-related mortality among women of reproductive age in South Africa is largely attributed to increased access to antiretroviral treatment resulting in non-communicable diseases such as diabetes, cerebrovascular disease and hypertension surpassing HIV as the leading causes of death. Although there appears to be higher risk of CVD in HIV infected men, international studies have shown that the risk of CVD in HIV infected women is significant. As more HIV infected South African women of reproductive age access antiretroviral treatment resulting in potential increased life expectancy, there remains a paucity of data for non-communicable co-morbidities in this vulnerable population group.

In addition to the well-recognized traditional risk factors for CVD in HIV uninfected women, there is increasing evidence of HIV-related chronic inflammation and immune activation and certain antiretroviral drugs that contribute to the increased presence of metabolic syndrome in PLWH. The presence of metabolic syndrome defined by elevated blood pressure, glucose, dyslipidaemia and abdominal obesity, doubles the risk of cardiovascular disease. A systematic review has shown that the mean prevalence of metabolic syndrome among PLWH in Africa was 30.5%. Local studies have demonstrated an increase in obesity in the first 3 years after HIV acquisition and that obesity is more pronounced in black females compared to males. Investigators have further demonstrated that South Africa is facing an epidemic of hypertension, and that there is a high prevalence of concurrent hypertension and HIV highlighting the need for improved integration of management guidelines. The Heart of Soweto study has shed light on the rising incidence of acute coronary syndrome and other cardiovascular diseases in Black South Africans.

Several studies have shown that majority of the non-nucleoside reverse transcriptase inhibitors (NNRTIs), including current 1^st^ line ART Efavirenz, and NRTIs, currently in use are associated with impaired lipid metabolism whereas the newer ART have not been associated with significant adipocyte dysfunction.

Methods of risk prediction and risk reduction strategies for atherosclerotic CVD in people living with HIV remain a major research gap in developing countries. A recent recommendation by the World Health Organization (WHO) is the provision of a cardiovascular risk assessment in all people living with HIV using standard protocols recommended for the general population. The commonly used cardiovascular risk assessment tools are non-specific to HIV and/or resource-constrained settings. The South African dyslipidaemia guidelines advocate CVD risk assessment at ART initiation by means of the Framingham table which underestimates risk in this population and is non-specific to LMIC. WHO Package of Essential Non-communicable Disease interventions for primary health care in low resource settings (WHO PEN) encompasses the WHO and International Society of Hypertension (WHO/ISH) cardiovascular risk prediction charts which are specific to 14 epidemiological sub-regions, and applying charts for sub-region Afr E would be a more suitable CVD risk assessment tool in our setting. In addition to the risk assessment, the WHO PEN provides concise management guidelines for CVD risk modification.

The association between HIV and CVD risk factors in South Africa has been documented mainly in cross-sectional studies. The WHO PEN is the investigator’s choice of intervention in this proposed prospective study in women who receive HIV care. There are currently no studies assessing the impact of WHO PEN interventions in people living with HIV in resource-constrained settings.

## Research Question/Hypothesis

An integrated model of HIV care, that includes the WHO PEN, will identify and modify risk factors in more women when compared to a HIV management plan that does not include screening and prevention of atherosclerotic cardiovascular disease.

# AIM and objectives

## Overall Aim

The overarching aim of the study is to determine the impact of including screening for prognostic markers of cardiovascular disease on the modification of cardiovascular risk factors in HIV positive women on ART.

## Specific Objectives

**Primary objectives:**

- Determine the effectiveness of the *WHO Package of Essential Non-communicable Disease interventions for primary health care in low resource settings* (WHO PEN), integrated with standard of care HIV management guidelines, in identifying and in modifying risk factors for atherosclerotic cardiovascular disease in women receiving HIV care.
- Compare cardiovascular disease (CVD) risk scores using the WHO PEN *WHO/ISH Cardiovascular risk prediction chart for WHO epidemiological sub region AFR E*, *Data collection on adverse effects of anti-HIV drugs study (DAD risk assessment) and Framingham risk assessment* with short-term cardiovascular disease outcomes (presence of subclinical atherosclerosis by means of CMIT, presence of CVA, Myocardial infarction, Angina) in women aged over 40 years.

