# research design and methods

## Overview

1. Study Setting: Umlazi/Philasande Research Clinic and Gateway Umlazi Clinic
2. Study Design: This study is a prospective two-arm, quasi-experimental design comparing a primary health care intervention plan with usual care.
3. Target Population: HIV infected women attending PHC
4. Study population: HIV infected women aged from 18 to 49 years of age and receiving HIV care at PHC clinics.
5. Inclusion criteria

- HIV infected women
- On ART for at least 1 year
- Equal to/older than 18 years of age
- Equal to/younger than 49 years of age
- Plans to remain in the study catchment area for at least 3 years

1. Exclusion criteria

- Participant declines study participation

1. Sampling

• Size of sample

400 HIV-infected women consisting of an intervention arm of 200 women co-enrolled in the PROMOTE study at the Umlazi CRS (see method of sampling for details), and a control arm of 200 women receiving HIV care at the PHC. With a 20-30% estimated prevalence of metabolic syndrome in people living with HIV without any specific intervention in the risk factor modification of cardiovascular disease and a proposed 10-15% estimated incidence of metabolic syndrome in the intervention arm, 132 participants per arm would allow for 80% power. An additional 10% can be added to allow for loss to follow-up. The larger proposed sample size will allow for external validity / generalizability.

- Method of selecting sample

Two HIV-infected female cohorts will be matched for receipt of ART duration >1 year and for age will be compared in the study. Method of selection will be via convenience sampling.

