- **Intervention group**: The prevalence of CVD risk factors will be determined by data collection through history taking, physical examination, and laboratory and radiology investigations as per the data collection tool. CVD risk assessment will be performed annually using a combination of the WHO and International Society of Hypertension cardiovascular risk prediction (WHO/ISH) and the DAD CHD equation. The intervention proposed is a modified WHO PEN algorithm incorporated into HIV management guidelines at study entry. Trends in all risk factors will be monitored, and new risk factors identified, with 6 monthly intervention during the first year, and annually for three years thereafter.
- **Control group**: Following informed consent, data will be collected from the participants ARV clinic medical chart as per the data collection tool. Standard of care HIV management and primary health care will be provided by public sector clinic staff according to current national guidelines. No study investigations or study questionnaires will be carried out at entry visit until the final study visit. There will be regular telephonic follow up with the participants to maintain study retention. Chart review data collection at 6 monthly intervals. CVD risk factors, as per outcomes described above, will be measured by the study at a single 3 year final study visit. Information obtained will be conveyed to the clinic staff for further management if required.

1. Plan for Data handling/processing

- Data will be analysed using SAS or SPSS software

1. Statistical methods

- Descriptive statistics-continuous variables will be represented by means, medians, prevalence, standard deviation.

The categorical variables will be represented by N+%

- Analytic statistics

The continuous variables will be compared by use of t-tests or Wilcoxon rank sum tests.

The categorical variables will be compared using Chi sq or Fisher’s exact test/

- Logistic regression will be applied to identify predictors of cardiovascular disease between the two arms, and between those participants who exhibit atherosclerosis by carotid intima thickness and those who don’t.

1. List of possible confounders

- Women in the intervention group are already enrolled in a study with controlled settings. These women may have commenced ART with a higher baseline CD4 counts.
- Multivariate logression analyses will be utilized in order to control for confounders.

1. List of associations to be measured

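### The sample size and 80% power rest on metabolic syndrome, which the protocol never names as an endpoint, and primary objective 1 has no variable that decides it

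*Protocol*

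**What the plan says.** **Objective.** In Specific Objectives, the first primary objective is the effectiveness of WHO PEN, integrated with standard HIV care, "in identifying and in modifying risk factors for atherosclerotic cardiovascular disease in women receiving HIV care". The Research Question/Hypothesis section expects risk factors to be identified and modified in more women than under usual care. Neither text names a factor, a threshold, a composite or a time point.

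**Sample size.** In the Overview, under Sampling, the calculation begins "With a 20-30% estimated prevalence of metabolic syndrome in people living with HIV without any specific intervention" and sets this against "a proposed 10-15% estimated incidence of metabolic syndrome in the intervention arm". It concludes that "132 participants per arm would allow for 80% power" and adds "An additional 10% can be added to allow for loss to follow-up". The planned arms are "an intervention arm of 200 women co-enrolled in the PROMOTE study" and "a control arm of 200 women receiving HIV care at the PHC". Significance level and sidedness are not given.

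**Analysis.** Under Statistical methods, "The continuous variables will be compared by use of t-tests or Wilcoxon rank sum tests"; categorical variables get chi-square or Fisher tests. Logistic regression is aimed at cardiovascular disease and at atherosclerosis by carotid thickness. These are general instructions, and no variable is singled out.

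**Metabolic syndrome elsewhere.** It is described in the Background and in the Literature Review by four components (blood pressure, glucose, lipids, abdominal obesity), without cut-offs or a required number of components. It does not appear in the hypothesis, overall aim, objectives, variable schedule, statistical methods or association table.

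**The concern.** A power statement is useful only if it refers to the comparison that will decide the study. Here the only powered comparison is one that no section of the plan says will be made, and the objective it should support refers to risk factors as a group. Two consequences follow.

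- The 80% cannot be attached to the primary conclusion, whatever that conclusion turns out to be.
- With no deciding variable, the plan does not say what to conclude if some factors improve and others worsen, for example if blood pressure falls while BMI rises. It leaves room to rest the claim on whichever factor looks favourable.

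**Working it through.** **1. Reproduce the plan's figure.** Inputs from the Sampling item: control 20–30%, intervention 10–15%, 80% power, equal arms. Assumed: two-sided 5%.

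Formula: n per arm = [1.96·√(2p̄(1−p̄)) + 0.8416·√(p₁(1−p₁)+p₂(1−p₂))]² / (p₁−p₂)².

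For 30% versus 15%, p̄ = 0.225:
- 1.96·√0.34875 + 0.8416·√0.3375 = 1.1575 + 0.4889 = 1.6464
- 1.6464² / 0.0225 = 120.5, so 121 per arm
- with continuity correction, (n/4)·(1+√(1+4/(n·0.15)))² = 133.5, so 134 per arm

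The stated 132 is therefore close to the metabolic syndrome comparison at the upper end of both ranges. Other pairs inside the ranges need, without continuity correction, from 62 (30% versus 10%) to 906 (20% versus 15%) per arm.

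**2. Look for that comparison in the plan.**

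| Protocol section | Metabolic syndrome named? |
|---|---|
| Research Question/Hypothesis | No |
| Overall Aim; primary and secondary objectives | No |
| Variable schedule | No; waist, systolic BP, fasting glucose and lipogram are separate rows |
| Statistical methods | No |
| Association table | No |
| Sampling | Yes, the sole basis of the sample size |

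**3. Count the outcomes that objective 1 could refer to.** The schedule has 11 risk-factor rows measured in both arms at month 36: BMI, waist, systolic BP, pulse, glucose, lipogram, hsCRP, urine microalbumin, smoking, diet and exercise. Counting the lipogram as four lipids (an assumption, since the schedule does not list its parts) gives 14. Adding the three risk scores to the 11 rows also gives 14.

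**4. False-positive chance if any one result sufficed.** No true effect, each test at two-sided 5%. For independent tests:
- favourable direction only: 1−0.975¹¹ = 24%; 1−0.975¹⁴ = 30%
- either direction: 1−0.95¹¹ = 43%; 1−0.95¹⁴ = 51%

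For equally correlated test statistics, by simulation:

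| Correlation | 11 tests, favourable | 14 tests, favourable | 11 tests, either | 14 tests, either |
|---|---|---|---|---|
| 0 | 24% | 30% | 43% | 51% |
| 0.3 | 19% | 22% | 37% | 44% |
| 0.5 | 15% | 17% | 30% | 35% |
| 0.7 | 11% | 12% | 22% | 25% |

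One test gives 2.5% (favourable) or 5% (either). The documents give no correlations, so the whole range is shown.

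**5. Power if metabolic syndrome at month 36 were the deciding endpoint.** Power = Φ{[(p₁−p₂)√n − 1.96·√(2p̄(1−p̄))] / √(p₁(1−p₁)+p₂(1−p₂))}.
- 30% versus 15%, n = 200: (2.1213 − 1.1575)/0.5809 = 1.66, power 95%
- 20% versus 10%, n = 200: (1.4142 − 0.9897)/0.5 = 0.85, power 80%
- after 10% loss, 200 × 0.9 = 180 per arm: 93% and 76%

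**6. Can it be measured?** Waist, systolic BP, fasting glucose and fasting lipogram are scheduled in both arms at month 36. Before that visit, control women have chart review only, which does not list waist or glucose. Presence at month 36 can be compared between arms; new onset cannot be established for controls.

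**The case against.** The best defence is that metabolic syndrome summarises the very risk factors that objective 1 targets. Its components are all collected at month 36, and once it is derived the general categorical tests would cover it. On this view only a name and a rule are missing, and a statistical analysis plan that is not shown could supply them, together with the responder definition and multiplicity handling. The data collection tools are also not shown, so the syndrome may be recorded there.

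Part of this stands. The power figure is not for an unrelated outcome, and the absence of a multiplicity procedure is not in itself a fault in a protocol. What remains is that the objective and the sample-size basis are both fixed in this document and name different targets. A later plan could add detail but would not make those two sections agree.

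A reader might go further and infer that objective 1 can be declared met on any one of 14 factors, with a 51% false-positive rate. The documents do not support that. No section says one significant factor is enough, and the hypothesis speaks of more women, which points to a proportion. The count of 14 depends on splitting the lipogram or adding the risk scores. The 51% assumes independent tests and also counts results in which women on WHO PEN did worse, so it is not the rate of false claims of benefit.

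**Conclusion.** The point holds as a mismatch within the protocol. The sample size and 80% power belong to metabolic syndrome, no stated objective or analysis uses it, and objective 1 has no deciding variable, so the power does not apply to the primary conclusion. The inflation of false positives is conditional: it arises only if a single favourable factor is taken as success, which the plan neither states nor rules out. In that case it would be about 11–30% against 2.5% (about 22–51% against 5% in either direction). This rests on an assumed two-sided 5% level, 11 to 14 outcomes and equal correlations between 0.7 and 0. Even the lowest figure is more than four times the single-test rate.

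**What to change.** - **Specific Objectives:** name presence of metabolic syndrome at the month-36 visit (yes/no) as the endpoint that decides the modifying part of objective 1. Use one fixed component rule, the same in both arms, built from measurements already scheduled in both. Label the individual risk factors and the identifying part as secondary or descriptive.
- **Variable schedule and Statistical methods:** add the derived variable and its between-arm comparison.
- **Sampling:** state both arms' rates as month-36 prevalence, in place of a prevalence set against an incidence, and give the significance level and sidedness.

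The cost is protocol wording and one derived variable, with no extra participants or visits. The downside is that a favourable result on one risk factor can no longer carry the primary claim. If the sponsor prefers another primary variable, the sample size must be recalculated for it. The change does not deal with confounding between the two convenience-sampled, non-randomised arms, so the adjusted analysis already foreseen in the protocol is still needed. Nor does 200 per arm cover the smallest difference inside the stated ranges: 20% versus 15% needs 906 per arm.

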**Secondary objectives:**

- Compare CVD risk between women receiving Efavirenz versus Lopinavir/r containing ART regimens.

# LITERATURE REVIEW

## Introduction:

A Sciencedirect and Pubmed literature search of multi-national clinical trials, observational studies and systematic reviews all allude to the increasing incidence of cardiovascular disease (CVD) in HIV uninfected and infected populations in developed and developing nations, and in young and old([2-7](#_ENREF_2)). Traditional risk factors for CVD, namely genetic predisposition and behavioural risk factors such as the use of tobacco, excessive alcohol consumption, sedentary lifestyle, and inappropriate diet are well known in the general population, and are becoming more evident in people living with HIV (PLWH) in low and middle income countries (LMIC) due to poverty and emerging factors such as increased urbanization([8](#_ENREF_8)).

In African regions and other low and middle-income countries the increased access to antiretroviral treatment and treatment success is unfortunately accompanied by a rise in cardio-metabolic disease ([3](#_ENREF_3), [4](#_ENREF_4), [9](#_ENREF_9)). In addition to known traditional risk factors, HIV through direct mechanisms of persistent immune activation and chronic inflammation in an ageing treated HIV-infected population, and indirectly through the effects of antiretroviral treatment (ART), contribute to the increased presence of intermediate risk factors of CVD in PLWH ([5](#_ENREF_5), [10](#_ENREF_10)). The intermediate risk factors, namely elevated blood pressure and blood glucose, dyslipidaemia and abdominal obesity, make up an entity called metabolic syndrome and the presence of this syndrome doubles the risk of CVD. A systematic review has shown that the mean prevalence of metabolic syndrome among PLWH in developing countries was 30.5%, 21.5%, and 21.4% in Africa, Asia, and South America, respectively. The most common metabolic abnormality across all countries in this review was the presence of a low high-density lipoprotein ([6](#_ENREF_6)).

## HIV and Dyslipidamia

HIV-infected Black Africans, irrespective of ART use, have significantly higher total cholesterol (TC) to High density lipoprotein-cholesterol (HDL), and triglyceride to HDL-C ratios, compared with the HIV uninfected persons ([11](#_ENREF_11)). Untreated PLWH have low HDL cholesterol levels and high triglycerides depicted in a systematic review([12](#_ENREF_12)). South African guidelines on the management of lipid disorders in HIV infected individuals advocate a full lipogram and assessment of cardiovascular risk prior to initiation of ART ([13](#_ENREF_13)) however this is not routinely practiced. According to these guidelines, if elevated lipids are present, the most suitable ART should be selected and watchful use of statins or fibrates may be considered. In the event of dyslipidaemia requiring medical treatment in PLWH on a Protease inhibitor (PI), it is recommended to substitute the PI with an integrase inhibitor or other alternate cholesterol lowering agents to prevent adverse events such as myopathy. However, various studies now demonstrate that not only PIs, but the majority of the Non-nucleoside reverse transcriptase inhibitors (NNRTIs) and NRTIs currently in use are associated with impaired lipid metabolism whereas the newer antiretroviral agents have not been associated with significant adipocyte dysfunction ([5](#_ENREF_5), [14](#_ENREF_14)).

One of the most widely used ARVs in developing countries, Efavirenz (EFV), has been shown to adversely influence cholesterol levels by increasing TC, Low density lipoprotein (LDL) cholesterol, and triglycerides, and impair endothelial cell function, leading to the development of atherosclerosis ([15-18](#_ENREF_15)). Tenofovir disoproxil fumarate (TDF) - based ART had lower lipids compared with other NRTI([14](#_ENREF_14)). Dolutegravir (DTG) use caused no significant change in lipids in the SPRING-1 study ([19](#_ENREF_19)). With regards to management of lipid disorders, the European AIDS Clinical Society (EACS) as do many other guideline committees, advocate initiation of lipid lowering treatment if there is no improvement in cholesterol levels despite a modified diet ([20](#_ENREF_20)). There is an important role for treatment with statins in HIV infection and it is vital to be aware of the indications and contraindications to specific statin therapy within the context of HIV ([21](#_ENREF_21), [22](#_ENREF_22)).

## HIV and Hypertension

Investigators have demonstrated that South Africa is facing an epidemic of systemic hypertension ([23](#_ENREF_23)), another intermediate risk factor of CVD, and what is also been significantly demonstrated is a high prevalence of concurrent hypertension and HIV locally and internationally ([24-27](#_ENREF_24)). It has been shown that PLWH who are not on ART and persons treated with integrase inhibitors had lower systolic BPs than persons who were not on integrase inhibitors([28](#_ENREF_28)). Less than half of patients treated for HIV who had concurrent hypertension received treatment for hypertension in the HOPS study population ([29](#_ENREF_29)) and locally 40% of PLWH were uncontrolled on hypertensive therapy ([30](#_ENREF_30)), demonstrating the suboptimum management of the co-morbidity, hypertension, in PLWH.

